| 1. **Objectives, Specific Aims and Rationale**   *Objective*  To investigate the use of antibiotics and their protective effect against complications of infection to inform the development of risk prediction models to guide antibiotic treatment decisions for suspected infection in primary care.  *Aims*   1. Estimate the incidence of i) GP consultations for infection and ii) antibiotic prescriptions by: age-group, gender, SES, ethnicity, selected co-morbidities, obesity and smoking status 2. Describe antibiotic prescribing patterns linked to the reason for the prescription by: age-group, gender, SES, ethnicity, selected co-morbidities, obesity and smoking status 3. Estimate the incidence of adverse outcomes in the following 28 days including: hospital admission for infection; A&E admission; re-consultation for infection; re-consultation for antibiotic side-effects (rash, nausea, …) and death for patients with a GP consultation for i) respiratory tract infection ii) urinary tract iii) skin/soft tissue infection, comparing patients with each listed age/co-morbidity group (including smoking status and obesity) to non-comorbid patients 4. Estimate the number of patients needed to treat with antibiotics to avoid one infection-related adverse outcome, comparing the results for each age/co-morbidity group to non-comorbid patients 5. Develop risk prediction tools to support clinical decision making and communication with patients   *Rational*  We have previously shown that more than half of all antibiotic prescriptions in primary care are issued to less than 10% of patients, and that this 10% of patients have high levels of co-morbidity.1 Targeting such high-frequency users of antibiotics in antimicrobial stewardship programmes might provide opportunities for a more effective intervention approach. Underlying this hypothesis is the assumption that it might be safe and feasible to reduce prescribing in patients with the highest levels of antibiotic prescribing, many of whom have co-morbidity.  To investigate whether higher rates of antibiotic use are likely to be justified in higher risk patients compared to patients who lack these risk factors, we will undertake a series of studies to investigate which patients in terms of age, gender, SES, ethnicity, selected co-morbidities, obesity and smoking get the most antibiotics. We will determine which patients are most likely to receive antibiotics for which infections and relate this to national guidance on antibiotic prescribing. To estimate whether the protective effect of antibiotics differs according to the patient’s age and the presence of co-morbidity, obesity or their smoking status, we will estimate the risk of infection related adverse-outcomes, comparing patients who have been treated with antibiotics to those who have not been treated with antibiotics for each of these groups. We will use these estimates to calculate the number of patients who need to be treated with antibiotics to avoid one infection-related adverse outcome (NNT), accounting for age, gender, SES, ethnicity, co-morbidity, obesity and smoking status. This will inform the development and validation of individualised risk-prediction models to support clinical decision-making and patient communication around the need for antibiotic treatment for suspected infection in primary care. |

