| 1. **Exposures, Health Outcomes§ and Covariates**   **§***Please note:**Summary information on health outcomes (as included on the ISAC application form above) will be published on CPRD’s website as part of its transparency policy*  *Exposure*  Exposures will include i) prescription of an antibiotic ii) GP consultation for suspected infection (see Appendices: Table 1 – Codelist for antibiotics, Table 2 – Codelist categorising indications for antibiotic use and Table 3 – Codelists to identify patients with suspected respiratory tract, urinary tract or skin/soft tissue infection)  *Health Outcomes*  The following outcomes (within 28 days of presentation in primary care) will be separately considered for analysis:   - Re-consultation for the same type of infection (CPRD; see Appendix Table 3) - Re-consultation for a side effect of antibiotic treatment (CPRD; see Appendix Table 4a –side effects of antibiotic treatment) - Complications of infection in primary or secondary care (CPRD and inpatient HES; see Appendices: Table 4b and 4c – complications of infection; depending on the indication) - Admission to Accident & Emergency (HES A&E) - All-cause hospitalisation (inpatient HES) - All-cause mortality (CPRD, HES and ONS)   We will undertake a sensitivity analysis to investigate the impact of excluding outcomes that occur on the same day as the exposure. The impact of different time windows will be explored, informed by a literature review on the natural history of the duration of different infections.  *Covariates*  We will include the following covariates:   - Age (classified as 0-4, 5-17, 18-44, 45-64, 65-84, 85-94 and 95+, years of age inclusive) - Sex (female and male) - Index of Multiple Deprivation (IMD; 1-5) - Co-morbidities (coded as indicator variables based on national guidance from Public Health England3 and feasibility1; see Appendix Table 5 for comorbidity code list)   - Diabetes   - Chronic Kidney Disease (CKD)   - Chronic Obstructive Pulmonary Disease (COPD)   - Asthma - Obesity - Smoking status15 - Season (months or quarters) and year - Ethnicity   We will undertake a sensitivity analysis of the impact of coding co-morbidities as binary indicator variable and as total number of co-morbidities. |

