| 1. **Amendments**   **Adding additional covariates in line with previous literature**  Summary:  We would like to include the following additional covariates:   - - Coronary Heart Disease   - Stroke   - Heart Failure   - Peripheral Arterial Disease   - Liver disease   - Immunosuppression   - Composite (Charlson Comorbidity Index - CCI)   Reasoning:  We originally excluded cardiovascular co-morbidities, liver disease, immunosuppression and the CCI because of insufficient power to detect our main effects of interest, i.e. differences between co-morbidities in the number needed to treat (*N. Data/ Statistical Analysis*, step 4.). While this is still the case, we now believe that we do need to include these variables as covariates in our analysis in order to ensure unbiased results and comparability to results from previous literature1,16. In line with the original protocol, **no** attempt will be made to interpret their effect sizes with regards to the number needed to treat (steps 4.-5.), as sample size calculations have indicated low power.  **Additional analysis of confounding**  Summary:  Preliminary analysis has shown unexpected differences to previously published results. These differences could be due to differences in datasets used, differences in countries analysed, or differences in practices and patients included. We plan to further investigate the reasons for the observed difference to be able to present the findings in context.  Reasoning:  After performing analysis of steps 1. and 2. described in section *N.* Data/ Statistical Analysisand comparing them to previous studies on THIN, we found differences in reported rates of antibiotic prescribing and rates of incidence of infection. The size of these differences was up to 30% and persists even when identical code lists and procedures are used. We are not entirely clear why we see these differences, but they seem unlikely to be chance findings and may be clinically relevant, thus warranting further investigation. All previous studies were performed using UK-wide, primary care-only data. We speculate that differences arose because we limited our sample to England-only, HES-linked data. For example, a recent study suggested that i) there might be differences in antibiotic prescribing behaviour between UK countries, with England having lower rates of prescribing than its neighbours.16 These conclusions are in line with our findings, but alternative explanations exist: ii) there might be differences between practices that agree to link their data to HES and ONS as compared to those who don’t, iii) there might be differences between patients who opt out of linkage as compared to those who don’t, and finally iv) there might be differences in practices that contribute to THIN compared to those that contribute to CPRD. In order to be able to appropriately interpret and use the results of this study, we aim to investigate which of the above hypotheses is the most likely. We will rerun all analysis in steps 1. and 2. (which use only primary care) on all patients in CPRD, using the definitions in *K. Study population* but omitting criteria concerning data linkage (bullet points a., c. and the second half of d.). The results from these calculations will then be used to judge whether the observed differences are due to practices excluded because of their country (i), due to practices excluded because of linkage (ii), due to patients excluded because of linkage (iii), or due to practices which are not in CPRD at all (iv). |

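### The amendment puts the Charlson composite in the same covariate list as single conditions, so adjusted co-morbidity rate ratios in Objectives 1 and 3 may no longer compare with non-comorbid patients

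*Protocol*

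**What the plan says.** Section M of the protocol lists diabetes, CKD, COPD and asthma under "Co-morbidities (coded as indicator variables based on national guidance from Public Health England". It allows a summary measure only as another coding: "We will undertake a sensitivity analysis of the impact of coding co-morbidities as binary indicator variable and as total number of co-morbidities".

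The Amendments section then adds coronary heart disease, stroke, heart failure, peripheral arterial disease, liver disease, immunosuppression and "Composite (Charlson Comorbidity Index - CCI" in a single list of additional covariates. The reasoning covers the whole list: "we do need to include these variables as covariates in our analysis in order to ensure unbiased results". The amendment also rules out interpreting the added variables with regard to the NNT in steps 4 and 5. It sets no such limit on the original four co-morbidities, or on the rate ratios in steps 1 and 3.

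Aim 3 fixes the intended contrast: "comparing patients with each listed age/co-morbidity group (including smoking status and obesity) to non-comorbid patients". Aim 4 uses the same reference group for the NNT. Section N presents adjusted rate ratios for Objectives 1 and 3 from Poisson or negative binomial models with co-morbidity among the covariates. For Objective 5, it adds risk factors according to how significant they were in Objective 4.

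**The concern.** A composite co-morbidity index is built from conditions of the kind that the protocol also enters singly. With the index held fixed, a patient with diabetes is compared with a patient who has no diabetes but the same score, and who therefore has some other scored disease. A non-comorbid patient scores zero and cannot be the comparator for any condition that the index counts. The reported ratio then answers whether this condition is worse, point for point, than the rest of the index. Aim 3 asks whether patients with the condition fare worse than patients without co-morbidity.

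A reader of the adjusted rate ratios could conclude that a co-morbidity carries no excess rate of consultation, prescribing or adverse outcome, or even a lower one, when the true contrast is an increase. Shifted coefficients and wider standard errors could also change the order in which risk factors are considered for the prediction tool.

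**Working it through.** The protocol gives no figure that depends on this choice, so there is none to reproduce. The check is algebra plus an exact calculation over all combinations of conditions.

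**Algebra.** Let the index be S = Σ w_j x_j + w_u u, where the x_j are conditions with their own indicator and u is a scored condition without one. Let the true model be log rate = a + Σ b_j x_j + g u. Substituting u = (S − Σ w_j x_j)/w_u gives

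log rate = a + Σ [b_j − (w_j/w_u) g] x_j + (g/w_u) S.

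With S in the model, the ratio for condition j is therefore exp(b_j) / R^(w_j/w_u), where R = exp(g) is the ratio carried by the unlisted condition.

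**Inputs.** From section I: baseline risk 2.4%, antibiotic effect 0.69 and treatment-by-co-morbidity interaction 0.83, used here as rate ratios. Assumed, because the protocol does not give them: a true ratio of 1.30 for each of four listed conditions; prevalences of 6% (diabetes), 5% (CKD), 2% (COPD) and 5% (coronary disease); 5% for each unlisted condition; independent conditions; half of patients treated; index entered as a linear term.

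**Ratio for a condition whose true ratio is 1.30, with the index added**

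| Ratio R of unlisted conditions | 1.0 | 1.2 | 1.5 | 2.0 |
|---|---|---|---|---|
| Weight 1; one unlisted condition, weight 2: 1.30/R^0.5 | 1.300 | 1.187 | 1.061 | 0.919 |
| Weight 1; two unlisted conditions, weights 2 and 1 (Poisson fit) | 1.300 | 1.166 | 1.023 | 0.865 |
| Weight 1; one unlisted condition, weight 1: 1.30/R | 1.300 | 1.083 | 0.867 | 0.650 |
| Weight 2; two unlisted conditions, weights 2 and 1 (Poisson fit) | 1.300 | 1.046 | 0.804 | 0.576 |

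Without the index, every cell returns 1.30. Random simulations under other assumed prevalences and weights gave 1.14, 1.08 and 0.88 in one case and 1.19, 1.04 and 0.82 in another, for R = 1.2, 1.5 and 2.0 and a weight-1 condition.

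**Precision.** For a weight-1 condition, adding the index multiplied the standard error by about 1.1 with two unlisted conditions (weights 2 and 1), and by about 1.35 to 1.58 with one unlisted condition of weight 1. If every index item also had its own indicator, the index would be an exact sum of the other columns. In a five-condition example the design matrix had rank 8 for 9 columns, so the coefficients could not be estimated.

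**Antibiotic effect.** In every row above, the antibiotic ratio stayed at 0.69 and its interaction with COPD at 0.83, with or without the index. If the odds of treatment are instead assumed to rise by a factor exp(0.3) = 1.35 per condition, then at R = 2.0 with two unlisted conditions the antibiotic ratio is 0.709 without the index and 0.692 with it. The interaction stays at 0.83.

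**The case against.** *Joint entry is inferred.* The amendment names no model, marks the index as a composite, and follows a section M that treats a summary measure as an alternative coding. The detail could be settled in an analysis plan that is not at hand. This softens the point but does not answer it. The index shares one list and one justification with the single conditions, and no wording separates it, so joint entry is the plain reading.

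*The intended contrast is not lost.* Multiplying the index term back in recovers it. In the second row of the table at R = 2.0 the per-point ratio is 1.503, and 0.865 × 1.503 = 1.30. That is correct, but section N presents adjusted rate ratios and mentions no such step.

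*The index serves the main purpose.* Section I names the antibiotic effect and its interaction with co-morbidity as the main effects of interest, and the amendment's appeal to unbiased results follows a sentence about the NNT. This stands. A reader might infer that the index also biases the antibiotic odds ratio or the NNT, given that aim 4 speaks of "comparing the results for each age/co-morbidity group to non-comorbid patients". The documents do not support that. Neither antibiotic term was biased by adding the index, the index can reduce residual confounding, and a model's predicted risk for a patient includes the index term. Section O also obtains absolute risks through inverse probability weighting, where overlap among covariates does not cause this problem.

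*Items and weights are assumed.* This also stands. Nothing in the protocol shows that asthma, obesity or smoking score in the index. Crude and stratified results are untouched, and section O calls Objectives 1 to 3 descriptive.

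**Conclusion.** The point holds for adjusted co-morbidity coefficients. As written, the amendment leads to models in which those coefficients contrast patients with equal index scores, for each listed condition that the index counts. Under the assumptions shown, a true 1.30 falls to between about 1.2 and 0.8 with mixed index weights. It falls further if the unlisted condition has a low weight or the listed one a high weight, and does not shift if the unlisted conditions have no effect. Standard errors rise.

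The adjusted rate ratios of Objectives 1 and 3 are affected. Aim 1 states no non-comorbid reference group, but section N still reports adjusted ratios for it. Selection by significance in Objective 5 may be affected, if the Objective 4 models also hold both terms.

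Reversal is a possibility, not a prediction. It needs the condition to be less harmful per index point than the rest of the index. Exact collinearity would arise only if every index item had its own indicator, which the protocol does not show. Bias in the antibiotic effect, its interaction or the NNT is not shown.

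**What to change.** Add one sentence to the amendment: the Charlson index is not entered in any outcome model that also holds the individual co-morbidity indicators and whose co-morbidity ratios are reported. Keep the six new single conditions as covariates. Use the index in place of the indicators in section M's alternative-coding sensitivity analysis and for comparison with earlier literature. It may stay in the propensity score. State which conditions the index scores and with what weights, so that the overlap can be seen.

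The cost is a short text change. No new data are needed, and the reported models lose only a term that overlaps with those already in them.

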| 1. **Study population**   The study period will be from 1st April 2007 to 31st December 2015.  We will perform all analyses in patients that were eligible for all linkages and fulfil the following:   1. registered at a participating English practice prior to the transfer of identifiers to the trusted third party for matching for at least a year before their entry into the study 2. their practice is deemed to be contributing ‘up-to-standard' (UTS) data at study start date 3. they had a valid identifier for linkage (NHS number for ONS mortality and HES data, postcode for IMD) 4. they had not opted out or dissented from CPRD or the linkage scheme 5. individual record is of ‘acceptable' research quality as verified by the CPRD.   **Cohort 1**: Individuals who were registered with a GP contributing to CPRD between 1st April 2007 and 31st December 2015 and who have a complete record on age, gender and IMD are eligible for inclusion in this study (see *P. Plans for addressing missing data*). Patients must have been registered with their GP for at least one year before entering the study with the exception of children aged less than one year who will be assumed to be born into the Practice. Patients can enter the study late or leave the study early in order to include patients who died within the study period (who might be inherently less healthy). Patients enter the study population on the latest of the following dates: continuous registration with GP for 12 months or 1st April 2007. Where patients registered with their GP after the 1st April 2007, patients enter the cohort after 12 months of continuous registration. Patients exit the cohort on the earliest of the following dates: the date the patient died, the date the patient left the practice, or 31st December 2015.  Subsequent studies are nested within cohort 1 (see Error: Reference source not found):   1. Nested cross-sectional study: Patients within cohort 1 with at least one prescription of an antibiotic 2. Nested cohort studies of specific infection syndromes: Patients within cohort 1 with at least one GP consultation for a specific infection syndrome (respiratory, urinary, skin/soft tissue). For these cohorts, patients will enter the cohort on the day of the consultation for infection. Patients will leave the cohort on the earlier of: 28 days after initial consultation, death, transfer out of practice or 31st December 2015. Patients can enter and exit the cohort more than once. |

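### The amendment's re-run lifts the country, practice-linkage and patient-linkage restrictions together with no breakdown, so as written it cannot attribute the gap to hypothesis (i), (ii) or (iii)

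*Protocol*

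**What the plan says.** The amendment (Protocol, *Amendments*, *Additional analysis of confounding*) reports that rates of prescribing and infection differ from earlier THIN studies: "The size of these differences was up to 30% and persists even when identical code lists and procedures are used". The suspected cause is the sample restriction: "We speculate that differences arose because we limited our sample to England-only, HES-linked data". It lists four explanations: (i) country, (ii) practices that do or do not agree to linkage, (iii) patients who do or do not opt out of linkage, and (iv) THIN practices differing from CPRD practices.

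One new calculation is named. Steps 1 and 2 are repeated on the whole of CPRD, keeping the section K population rules with one relaxation: "omitting criteria concerning data linkage (bullet points a., c. and the second half of d".). The criteria concerned are:

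- a: "registered at a participating English practice prior to the transfer of identifiers to the trusted third party for matching". This one bullet carries both country and practice linkage.
- c: "they had a valid identifier for linkage (NHS number for ONS mortality and HES data, postcode for IMD"). This is a patient-level linkage condition.
- d: "they had not opted out or dissented from CPRD or the linkage scheme". The second half is patient-level dissent from linkage.

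The stated use is: "The results from these calculations will then be used to judge whether the observed differences are due to practices excluded because of their country (i"), followed in the same sentence by (ii), (iii) and (iv).

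**The concern.** The amendment sets out to find which explanation is most likely, so that the study's results can be interpreted and used properly. Three of the four explanations concern different groups of excluded patients, and all three groups enter the data in the same step. The text gives no stepwise relaxation, no stratification by country or linkage status, and no separate analysis of the added groups.

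Nothing elsewhere supplies the split. *Study Design* lists the stratifiers and adjusters for all steps as age, gender, SES, ethnicity, co-morbidity, obesity and smoking. Steps 1 and 2 in *N. Data/ Statistical Analysis* add neither country nor linkage status. The practice random effect in step 1 allows for clustering but estimates neither contrast. The graphical look at practice variation in *O. Plan for addressing confounding* is aimed at coding differences and outlying practices.

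What is at stake is a reported choice among (i), (ii) and (iii) that the analysis cannot support. The risk is practical: the amendment already notes that lower prescribing in England would agree with its findings, so a higher all-CPRD rate could easily be read as confirming (i).

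**Working it through.** The plan states no figure for this re-run, so there is none to reproduce. The question is whether the quantities to be judged can be recovered from the quantities to be calculated.

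**Groups in the re-run**

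1. linkage-eligible patients of linked English practices (already analysed)
2. other patients of those practices, relevant to (iii)
3. patients of unlinked English practices, relevant to (ii)
4. patients of practices in other UK countries, relevant to (i)

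**Formula.** Let w_k be the share of group k and RR_k its rate ratio against group 1. Then

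pooled rate / linked rate = 1 + w2(RR2 − 1) + w3(RR3 − 1) + w4(RR4 − 1).

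The existing analysis gives the group 1 rate and the re-run gives the pooled rate. That is two equations for four group rates (rank 2 of 4), so RR2, RR3 and RR4 are not identified whatever the shares. Repeating this within age, sex or co-morbidity strata repeats the same problem in each stratum. Reporting rates for the four groups, or lifting the restrictions one at a time, gives rank 4 of 4.

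**Illustration 1.** The documents give no shares. Assume w1 = 50%, w2 = 5%, w3 = 20%, w4 = 25%.

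| Truth | Pooled / linked |
|---|---|
| only group 4 differs, RR 1.60 | 1 + 0.25 × 0.60 = 1.15 |
| only group 3 differs, RR 1.75 | 1 + 0.20 × 0.75 = 1.15 |
| group 3 RR 1.375 and group 4 RR 1.30 | 1 + 0.20 × 0.375 + 0.25 × 0.30 = 1.15 |

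These are three different explanations with one result. The rate ratios were chosen to show this and are not estimates.

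**Illustration 2: range.** Suppose the pooled rate is 10% above the linked rate. The rate ratio needed if one group alone is responsible is 1 + 0.10/w_k:

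- (i), w4 = 10–25%: 1.40 to 2.00
- (ii), w3 = 10–20%: 1.50 to 2.00
- (iii), w2 = 5–10%: 2.00 to 3.00

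The ranges for (i) and (ii) largely overlap, so the size of the pooled shift does not point to one of them.

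**Illustration 3: cancellation.** With w4 = 25% and w3 = 15%, a country RR of 1.20 adds 0.25 × 0.20 = 0.05. An unlinked-practice RR of 0.67 removes 0.15 × 0.33 = 0.05. The pooled rate does not move although both effects are present.

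**Illustration 4: linked against whole set.** If every excluded group has a 30% excess, the pooled rate exceeds the linked rate by (1 − w1) × 0.30. That is 15% at w1 = 50% and 7.5% at w1 = 75%. This matters only if the all-CPRD rate is compared directly with the linked rate.

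**IMD.** *K. Study population* requires a complete IMD record for cohort 1, and *P. Plans for addressing missing data* admits only records with SES. *Data Linkage Required* lists IMD among the linked data, and criterion c ties it to a postcode identifier. The amendment does not name this requirement among those omitted. Read literally, patients without IMD stay out, and these may be the very patients the re-run is meant to add.

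**The case against.** The strongest reply is that the amendment never says the re-run yields one pooled rate. It names the excluded groups to be judged, widening the data set is the necessary first step, and tabulation by group could be left to a later plan. It is true that pooling is inferred, and the data would presumably allow the split. But the protocol fixes both an analysis and the conclusion to be drawn from it, and neither the amendment nor the steps being repeated contain a country or linkage term. Followed as written, the conclusion does not follow.

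Three stronger readings are tempting and should not be adopted.

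- *Keeping the linked patients in is a mistake.* It is not. The earlier studies were UK-wide and used primary care data only, so unrestricted CPRD is the like-for-like comparator, and it is needed to test (iv). The dilution in Illustration 4 affects only a direct linked-against-whole comparison, which the protocol does not specify.
- *No practice outside England can be linked, so country must be judged among unlinked practices only.* The documents do not say this; they say only that this study required English practices.
- *Group 4 against group 3 is therefore the right country contrast.* It can mislead, because unlinked English practices may be selected on declining linkage. Suppose there is no country effect, and everywhere 70% of practices are of the agreeing type (rate 1.0) and 30% of the declining type (rate 1.3). Both countries then have rate 0.70 × 1.0 + 0.30 × 1.3 = 1.09. England against elsewhere correctly gives 1.00, but group 4 against group 3 gives 1.09/1.30 = 0.84, a false country effect. These values are assumed.

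**Conclusion.** The point holds in limited form. As specified, the re-run can show whether removing all restrictions closes the gap of up to 30%. Unless effects cancel, that informs (iv) against (i) to (iii) jointly. It cannot attribute the gap to country, practice linkage or patient linkage.

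Non-identifiability does not depend on any assumed number. It rests on reading the amendment as one re-run without a breakdown, which is what the text describes. The shares and rate ratios above are illustrations only; the documents supply none.

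A reader might infer that the treatment-effect or prediction results are undermined. The documents do not support that: the re-run concerns descriptive steps 1 and 2 and how they compare with earlier work.

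**What to change.** Keep the all-CPRD re-run as the comparator for the earlier UK-wide studies, and add to the amendment:

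- Report steps 1 and 2 by the four groups defined above, with rate ratios and 95% confidence intervals for step 1 and proportions with intervals for step 2.
- Read (iii) as group 2 against group 1, (ii) as group 3 against groups 1 and 2 combined, and (i) as group 4 against all English practices (groups 1 to 3). Give group 4 against group 3 only as a sensitivity contrast.
- State that the complete-IMD requirement is waived for this re-run. Fit the models without IMD adjustment, or with and without it where IMD is available.

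The cost is a four-level term in models already planned, a country and linkage indicator (which the amendment's own hypotheses presuppose can be identified), and a few sentences of wording. The downsides are wide intervals for the smallest group and weaker adjustment for SES.
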